### 3.11. Quality Control

We want to highlight that it is important to conduct quality control procedures to ensure the existence and accuracy of records. Quality control can be conducted using the INSIGHT level 1–3 data quality checks [43]. Briefly, level 1 verifies data completeness, level 2 ensures data consistency and level 3 checks for study variables and whether data are fit for purpose.

### 3.12. Protection of Human Subjects

Ethical considerations are paramount in any research involving human subjects. In this generic protocol for a retrospective database study, we describe data that exist in a deidentified/pseudonymised structured format without including personal patient information, thus eliminating the need for informed consent from participants. However, in the event of conducting a new study, it is essential to adhere to ethical guidelines and obtain approval and consent to safeguard the rights and well-being of participants if needed. There must be prospective approval from relevant Institutional Review Boards or Ethics Committees for the study protocol and amendments. Furthermore, we highly recommend conducting the study according to the guidelines for Good Pharmacoepidemiology Practice and the European Network of Centres for Pharmacoepidemiology and Pharmacovigilance (ENCePP) guide on Methodological Standards in Pharmacoepidemiology [44,45]. Additionally, the study protocol should be registered before data collection begins and adhere to transparency and scientific independence principles outlined by the ENCePP Code of Conduct [46].

## 4. Discussion

This generic protocol has been developed to assess the safety of RSV vaccines in pregnant women and their offspring in real-world settings utilising secondary sources of data. It presents the emulation of a target trial, assessing the safety of administering a single dose of an RSV vaccine to pregnant women between 24–36 weeks of gestation compared to pregnant women who do not receive RSV vaccination during pregnancy [8]. The emulation of target trial conditions will help to reduce bias due to censoring, immortal time, competing events and confounding, improve the interpretability of estimands and highlight any remaining challenges with the data [17]. However, despite efforts to minimise bias and improve interpretability, limitations persist in target trial emulation using observational data. These may include challenges in accurately capturing all relevant confounders. Data sources that routinely collect data often provide comprehensive information on treatments and outcomes but may lack sufficient detail on clinical factors that require adjustment [47]. Fitness for purpose of data can be assessed in feasibility studies [18,19].

The study will use code lists or observations in birth registers to identify the covariates and outcomes of interest. An important consideration of using code lists is the potential for outcome misclassification, which can introduce bias and impact the interpretation of findings. The code lists could be sourced from Vaccine Monitoring Collaboration for Europe (VAC4EU) (https://vac4eu.org/), as these have undergone thorough review by medical professionals. Only codes labelled as “narrow” are included to mitigate the false-positive rate. For preterm birth, validation may be needed since preterm birth can either be spontaneous or medically indicated (iatrogenic), whereas our focus is only on spontaneous preterm birth. Codes and outcome definitions may be scrutinised in Safety Platform for Emergency Vaccines companion guides. Validation of outcomes, using Brighton or WHO definitions, may be conducted when resources are available.

In addition to outcome misclassification, it is also crucial to address exposure misclassification. Since RSV vaccination has only recently received approval for maternal immunisation, and many countries’ National Immunisation Technical Advisory Groups have yet to decide on its inclusion in routine immunisation schedules, it can be challenging to determine whether current data sources accurately capture RSV vaccination. This challenge is reflected by the current situation in Europe, where other maternal immunisation practices vary widely across countries, and some prefer to provide monoclonal antibodies or vaccines to neonates [2,48] Therefore, before commencing data collection, it is imperative to liaise with relevant public health organisations to understand if and how RSV vaccination will be integrated into routine immunisation programs for maternal immunisation and in which settings it is provided. Subsequently, it is essential to verify if the data source adequately captures this information and compare it with national statistics to ensure comprehensive coverage and prevent exposure misclassification in the comparator group.

It is important to note that a non-exposed comparator group may be chosen because presently there is only one approved maternal vaccine for preventing RSV infection in offspring. In the event that other RSV vaccines receive approval, it is crucial to consider their inclusion in the study design. This necessitates either incorporating all different RSV vaccines in the exposed group or excluding women specifically vaccinated with other RSV vaccines from the unexposed group.

Because of safety concerns, the primary outcome measure under examination is preterm birth, considering the varying recommendations by EMA, FDA and MHRA regarding the optimal gestational age for vaccination [5,6,7,12,13]. Notably, concerns over preterm births have led to the suspension of a phase 3 trial for another candidate RSV prefusion subunit vaccine [10]. However, a significant challenge in analysing preterm birth in observational studies lies in its direct relationship with gestational age at the time of vaccination. For instance, administering the vaccine at 35 weeks of gestation cannot result in an preterm birth of less than 35 weeks. Therefore, we emphasise the critical importance of matching participants based on gestational age at the time of vaccination. In fact, participants will be enrolled in a sequence of weekly trials based on their gestational age at the time of vaccination. Additionally, we have added the outcome time between vaccination and birth. This outcome holds more statistical power than preterm birth, as preterm birth is a categorical outcome while time between vaccination and birth is continuous. Also, this approach allows us to examine the median time between vaccination and preterm births, which is crucial for identifying specific underlying mechanisms. For instance, it can reveal whether preterm infants are born days, weeks, or months after vaccination. Moreover, this outcome is independent of the accuracy of gestational age assessment [21,22]. Other outcomes can be chosen, and we refer to the GAIA initiative, which defined more than 20 outcomes relevant to maternal immunisation [31].

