### 3.9. Study Size

All women meeting eligibility criteria during the study observation period should be included in the study. It is currently unknown how many women will receive RSV vaccination during pregnancy, as the National Immunisation Technical Advisory Groups need to determine whether this will be included in routine maternal immunisation programs in the country or region where the study is conducted. Minimal detectable risks can be calculated based on the assumption that every vaccinated pregnant individual could be compared with N unvaccinated pregnant individual(s) (1:N ratio). The desired alpha level is 5%, and risk ratio (RR) values of 1.5, 2.0, 2.5, and 4.0 may be considered (Supplementary Table S2). For pregnancy and birth outcomes, the required number of exposed women to achieve a power of 80% under different RR values may assume prevalence rates in the unexposed group ranging from 0.2% to 6.0%. To detect an RR of 1.5 with 95% confidence interval (CI) for preterm birth, approximately 1200 pregnancies ending in live birth would need to be included in a data source. For rare outcomes during pregnancy such as GBS, we calculated the power obtainable assuming a maximum sample size of 30,000 exposed pregnant women, with an incidence rate of 1/100,000 person-years in the comparator group [39].

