#### 3.10.2. Measures of Effect

Primary analyses should estimate counts, proportions, and risk or rate ratios with 95% CI for events occurring and measurable during pregnancy, and counts, proportions, and prevalence ratios with 95% CI for outcomes measurable at birth. Comparison of outcomes by exposure status should be conducted using multivariable generalised linear models. These analyses should control for potential confounding by matching. Balance of covariates should be analysed using standardised mean differences (SMDs), some characteristics and risk factors for the exposure or outcomes may remain unbalanced, which should be analysed using plots of SMDs. To address this, propensity score methods can be employed and propensity scores can be adjusted or additionally matched on if necessary [40]. To obtain more power for the analysis of preterm birth, we recommend that time from vaccination to birth should be analysed separately [21,22].

The primary analyses may face-selective censoring due to treatment crossover in the comparator cohort, necessitating the use of inverse probability censoring weights. To maintain statistical power, unexposed pregnant women in the matched comparator cohort should be censored upon treatment violation, while exposed pregnant women should not be censored. Weights can be used to correct for the bias introduced by such censoring, ensuring more accurate and reliable results. Additionally, a sensitivity analysis can be conducted to explore the effect of censoring the matched pair if treatment crossover happens in the previously unexposed pregnant woman. Another sensitivity analysis may be carried out to explore the effect of exclusion of medically indicated iatrogenic births.

For subgroup analyses, secondary analyses can be conducted among immunocompromised or high-risk pregnancies and stratified by weeks of gestation at the time of vaccination.

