Follow-up period	For each maternal participant, including her fetus, data on adverse events were collected from the time of informed consent to 1 month after injection, and data on serious adverse events were collected from the time of informed consent through 6 months after delivery. Safety end points in the infant participants included adverse events from birth to 1 month of age. Additional safety end points were serious adverse events and newly diagnosed chronic medical conditions from birth through 12 to 24 months of age. For vaccine efficacy outcomes in infants started at 72 h after birth and continued through 12 to 24 months of age.	Follow-up of the exposed and unexposed (or active comparator) pregnant women should start on the day after eligibility criteria are fulfilled and end at the earliest of N months after birth depending on the outcome being measured, maternal death, disenrollment or migration, end of data availability in the data source, treatment crossover, or occurrence of a given outcome. Follow-up of offspring to assess birth outcomes will depend on the risk window for measuring the outcome and will end at the earliest of N months of age, neonatal death, disenrollment or migration, end of data availability in the data source, or occurrence of a given outcome.
Outcome	Safety: The primary safety end points were reactogenicity and adverse events in the maternal participants and adverse events and newly diagnosed chronic medical conditions in the infants. Efficacy: The two primary efficacy end points were medically attended severe RSV-associated lower respiratory tract illness and medically attended RSV-associated lower respiratory tract illness.	For post-authorisation safety study purposes, the focus is solely on safety, encompassing preterm birth, stillbirth, hypertensive disorders of pregnancy, low birth weight (LBW), small for gestational age (SGA), and Guillain-Barré Syndrome (GBS).
Causal Contrasts of Interest	Per protocol analysis	Observational analog of per-protocol effect
Analysis	Per protocol analysis	Same per-protocol analysis, except for restriction to pregnancies without loss-to-follow up

**Table 2 vaccines-13-00272-t002:** Outcomes of interest.

Outcomes	Clinical Definition	Pregnancies Among Which the Outcome Will be Ascertained	Exposure Risk Window for Outcome

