**Pregnancy outcomes**			
Preterm birth [23]	Preterm birth is defined by the WHO as babies born alive before 37 weeks of pregnancy are completed. It is further subcategorised based on gestational age: Extremely preterm (less than 28 weeks) Very preterm (28 to less than 32 weeks) Moderate to late preterm (32 to 37 weeks)	Pregnancies ending with live births	From time of vaccination to before week 37 of gestation (36 weeks and 6/7 days)
Time between vaccination and birth	Time between vaccination and birth in days.	Pregnancies ending with live and non-live births	From time of vaccination to time of birth
Stillbirth [24]	Stillbirth is defined by the WHO as the death of a foetus that has reached a birth weight of 500 g, or if birth weight is unavailable, gestational age of 22 weeks or crown-to-heel length of 25 cm. It is further subcategorised based on gestational age: Late foetal deaths (greater than 1000 g or after 28 weeks) Early foetal deaths (500–1000 g or 22–28 weeks)	Pregnancies ending with live and non-live births	From time of vaccination to end of pregnancy

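### The primary outcome, preterm birth, has two incompatible definitions: Table 2 counts every live preterm birth, the Discussion only spontaneous ones

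*Protocol article*

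**What the plan says.** Section 4 (Discussion) states that "the primary outcome measure under examination is preterm birth", with no restriction by type. Three places then say which births count.

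- Table 2: "Preterm birth is defined by the WHO as babies born alive before 37 weeks of pregnancy are completed". It is ascertained among pregnancies ending in live birth. The subcategories are by gestational age only; spontaneous or indicated onset plays no part.
- Section 3.10.2: "Another sensitivity analysis may be carried out to explore the effect of exclusion of medically indicated iatrogenic births". Removal is optional and a sensitivity analysis, so the main analysis contains these births.
- Section 4, in the paragraph on code lists and misclassification: "preterm birth can either be spontaneous or medically indicated (iatrogenic), whereas our focus is only on spontaneous preterm birth".

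The outcome row of Table 1 also lists the outcomes without restricting the first: "preterm birth, stillbirth, hypertensive disorders of pregnancy, low birth weight (LBW), small for gestational age (SGA), and Guillain-Barré Syndrome (GBS").

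Two neighbouring outcomes in Table 2 matter here. Hypertensive disorders of pregnancy are a separate outcome with a risk window running from vaccination until the pregnancy ends. Time between vaccination and birth covers live and non-live births with no split by type of delivery.

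**The concern.** A team that builds its outcome algorithm from Table 2 and a team that builds it from the Discussion would count different events under the same name. The article is a template meant to align studies, so the ambiguity would be passed on to each study that uses it. If the choice is left until data are in hand, it can affect the conclusion on the signal that motivates the study.

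The choice also bears on bias. Whether a delivery is indicated is determined after Time zero. If vaccination raised the incidence of hypertensive disorders, and some of these led to early delivery on medical indication, a spontaneous-only outcome would discard those preterm births. Matching does not prevent this: for the current pregnancy, the high-risk definition in Table 3 counts only conditions present before vaccination. The plan does not itself say that hypertensive disease leads to indicated delivery, so this pathway is a possibility raised here and not a statement of the document.

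**Working it through.** **1. The plan's own figure.** Section 3.9 says about 1200 pregnancies ending in live birth are needed to detect a risk ratio (RR) of 1.5 for preterm birth. It gives alpha 5%, power 80%, unexposed prevalences from 0.2% to 6.0% across outcomes, and a ratio 1:N with N open. It does not say which prevalence or N belongs to preterm birth. I take alpha as two-sided and 1200 as exposed women. With p0 the unexposed risk, p1 = 1.5 × p0, k unexposed per exposed woman and p̄ the weighted mean risk:

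n exposed = [1.96 × √((1 + 1/k) p̄(1 − p̄)) + 0.8416 × √(p1(1 − p1) + p0(1 − p0)/k)]² / (p1 − p0)²

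- p0 = 6%, k = 1: p1 = 9%, p̄ = 7.5%; (0.7301 + 0.3130)² / 0.03² gives 1209.
- p0 = 4%, k = 3: p1 = 6%, p̄ = 4.5%; (0.4692 + 0.2214)² / 0.02² gives 1193.

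Both agree with the stated 1200. The figure therefore does not show whether a total or a spontaneous-only prevalence lies behind it.

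**2. The statements side by side.**

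| Place | Indicated preterm births in the main analysis? |
|---|---|
| Table 2 | Yes: any live birth before 37 completed weeks |
| Section 3.10.2 | Yes: removed only in an optional sensitivity analysis |
| Section 4, naming the primary outcome | No restriction stated |
| Section 4, code-list paragraph | No: spontaneous only |

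If the last row governs, exclusion is the main analysis and cannot also be a sensitivity analysis. If the first two govern, the last row is wrong.

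**3. What a spontaneous-only outcome could miss.** The plan gives no share of indicated births. Assume a share q of 20% to 50%, an effect of vaccination on indicated preterm birth only (RR_ind), and an unchanged risk of spontaneous preterm birth. Then

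RR for all preterm birth = (1 − q) + q × RR_ind.

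| q | RR_ind = 1.5 | RR_ind = 2.0 | Spontaneous only, all women in the denominator |
|---|---|---|---|
| 20% | 1.10 | 1.20 | 1.00 |
| 30% | 1.15 | 1.30 | 1.00 |
| 40% | 1.20 | 1.40 | 1.00 |
| 50% | 1.25 | 1.50 | 1.00 |

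**4. Removing the women from the denominator as well.** With an assumed total unexposed preterm risk of 6%, the spontaneous-only RR becomes (1 − 0.06q) / (1 − 0.06q × RR_ind). For RR_ind = 2.0 this is 0.988/0.976 = 1.01 at q = 20% and 0.970/0.940 = 1.03 at q = 50%. For RR_ind = 1.5 it is 1.01 to 1.02. Dropping the women adds only a small distortion here; the main loss is that the events are no longer counted.

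**The case against.** The best defence is that the operative text agrees with itself. Table 2, the outcome row of Table 1 and section 3.10.2 all point to preterm birth of any type, and the outlier is one clause in the Discussion explaining why validation may be needed. On that reading no indicated birth leaves the primary analysis and the loss in step 3 never occurs. This stands in part: the loss is conditional on the Discussion clause being followed. It does not remove the contradiction, because that clause tells a team which preterm births are true cases and the article does not say which statement takes precedence.

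A reader might infer that the study would be unable to see harm running through hypertensive disease. The document does not support that. Hypertensive disorders are an outcome in their own right, and earlier delivery on indication would shorten the time from vaccination to birth, which section 3.10.2 recommends analysing separately. What would be lost is the resulting preterm births in the primary outcome.

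A reader might also infer that 1200 leaves a spontaneous-only analysis short of 80% power. Step 1 shows why this cannot be said: the prevalence and matching ratio behind 1200 are not stated, and 4% with three unexposed women per exposed woman fits as well as 6% with one. Section 3.9 also includes all eligible women, so 1200 is not a fixed enrolment.

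Finally, separating spontaneous from indicated births is not free. No passage promises that delivery type is recorded, and the Discussion makes outcome validation depend on resources.

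**Conclusion.** The definition of the primary outcome is wrong as written: Table 2 and section 3.10.2 include indicated preterm births, and the Discussion excludes them. This rests on the text alone and needs no assumption.

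The possible consequence is conditional. If the Discussion clause governed, an effect that doubled only indicated preterm births would give an RR of 1.2 to 1.5 for all preterm birth and about 1.0 for spontaneous preterm birth; with an effect of 1.5 on indicated births the all-cause RR would be 1.10 to 1.25. These figures rest on an assumed indicated share of 20% to 50% and an unchanged spontaneous risk, and they illustrate the mechanism without estimating it. No conclusion about power follows.

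**What to change.** - **Section 4:** state that the primary outcome is preterm birth of any type among live births, as in Table 2, and replace the clause that "preterm birth can either be spontaneous or medically indicated (iatrogenic), whereas our focus is only on spontaneous preterm birth" with wording that makes spontaneous preterm birth a secondary or sensitivity outcome.
- **Section 3.10.2:** where the data source records delivery type, keep women with an indicated preterm delivery in the denominator of the spontaneous analysis, for example as a competing event, instead of excluding them.
- **Section 3.9:** say which definition of preterm birth the assumed prevalence refers to, and the matching ratio used for the 1200.

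The first and third changes are wording only. The second costs one extra analysis, whose value depends on how well each data source classifies delivery type; where it cannot, the primary analysis is unaffected.

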## 5. Conclusions

This generic protocol is designed to offer guidance for researchers and health authorities in evaluating the safety of RSV vaccination during pregnancy. A target trial emulation approach of observational data can be selected to minimise bias and improve interpretability. We envision this protocol serving as a valuable tool, fostering alignment of research efforts and aiding in the monitoring of the safety of RSV vaccination in pregnant women and their offspring.

## Figures and Tables

**Figure 1 vaccines-13-00272-f001:**
[figure not shown]
Study design. * Matching should be on gestational age (same week of gestation), calendar time (same week) and maternal age. Additional characteristics may be added.

**Table 1 vaccines-13-00272-t001:** A summary of the protocol of the MATISSE trial and emulation of this target trial to estimate the effect of RSV vaccination during pregnancy.

Protocol Component	Target Trial	Emulation
Eligibility criteria	Healthy women, 49 years of age or younger, at 24 through 36 weeks’ gestation on the day of planned injection, with an uncomplicated, singleton pregnancy and no known increased risk of pregnancy complications.	We maintain the 24 through 36 weeks gestation requirement but do not apply strict age restrictions or restrictions regarding pregnancy complications. Instead, we stratify the analysis based on high-risk pregnancies.
Treatment strategies	(1) A single intramuscular injection of 120 μg of RSVpreF vaccine (60 μg each of RSV A and RSV B antigens) (2) Placebo	(1) RSV vaccination (2) No RSV vaccination
Assignment procedures	Women were randomly assigned in a 1:1 ratio to receive either the RSV vaccine or a placebo, and they were not aware of the strategy to which they had been assigned.	Exposed women will be matched to unexposed women (1:N ratio) based on: Gestational age (same week of gestation) Calendar time (same week) Maternal age (year of birth) Immunocompromised status High-risk pregnancy
Follow-up period	For each maternal participant, including her fetus, data on adverse events were collected from the time of informed consent to 1 month after injection, and data on serious adverse events were collected from the time of informed consent through 6 months after delivery. Safety end points in the infant participants included adverse events from birth to 1 month of age. Additional safety end points were serious adverse events and newly diagnosed chronic medical conditions from birth through 12 to 24 months of age. For vaccine efficacy outcomes in infants started at 72 h after birth and continued through 12 to 24 months of age.	Follow-up of the exposed and unexposed (or active comparator) pregnant women should start on the day after eligibility criteria are fulfilled and end at the earliest of N months after birth depending on the outcome being measured, maternal death, disenrollment or migration, end of data availability in the data source, treatment crossover, or occurrence of a given outcome. Follow-up of offspring to assess birth outcomes will depend on the risk window for measuring the outcome and will end at the earliest of N months of age, neonatal death, disenrollment or migration, end of data availability in the data source, or occurrence of a given outcome.
Outcome	Safety: The primary safety end points were reactogenicity and adverse events in the maternal participants and adverse events and newly diagnosed chronic medical conditions in the infants. Efficacy: The two primary efficacy end points were medically attended severe RSV-associated lower respiratory tract illness and medically attended RSV-associated lower respiratory tract illness.	For post-authorisation safety study purposes, the focus is solely on safety, encompassing preterm birth, stillbirth, hypertensive disorders of pregnancy, low birth weight (LBW), small for gestational age (SGA), and Guillain-Barré Syndrome (GBS).
Causal Contrasts of Interest	Per protocol analysis	Observational analog of per-protocol effect
Analysis	Per protocol analysis	Same per-protocol analysis, except for restriction to pregnancies without loss-to-follow up

**Table 2 vaccines-13-00272-t002:** Outcomes of interest.

Outcomes	Clinical Definition	Pregnancies Among Which the Outcome Will be Ascertained	Exposure Risk Window for Outcome
